**Fig. 4 Fig4:**
[figure not shown]
Bend and Squat device used to determine knee joint angle during wall squat exercise

Once the device is set to the participants personal wall and floor measurements necessary to replicate the angle required to elicit 95% HR_peak_, they will then be asked to squat in this set position as a fidelity check to ensure that it equates to their specific training knee joint angle. In the unlikely event that it is necessary, a slight adjustment to the wall height can be used to achieve the correct knee joint angle prescribed. Before the client leaves the surgery to commence their training, it will be ensured that they are completely confident with the information they have received. *Participants will then given a web link (USB stick if required) containing video instructions of how to set up their HR monitor, use the Bend and Squat device to perform a IE training session and how to record the necessary training data in their diaries*. They will also be provided with the study research assistant contact telephone and e-mail helpline address for use during office hours.

All IE training sessions thereafter will be completed in the home. Participants will use their Bend and Squat device to perform an IE training session composed of 4 bouts of 2-min wall squats with 2 min recovery in between each bout [60]. Participants will be instructed to perform three IE training sessions a week, ideally on alternate days to allow for adequate between session recovery. During the IE training sessions, the HR value displayed at the end of each 4 × 2-min wall squat along with their RPE will be recorded for subsequent analysis. If the mean HR of the four exercise bouts deviates from the prescribed THRR on two consecutive sessions in the first week of IE training (acting as a fidelity check), the knee joint angle and thus their Bend and Squat set-up will be altered accordingly based upon further interpolation of their HR/knee joint angle relationship.

### Criteria for discontinuing or modifying allocated interventions

Modification of the isometric exercise prescription will be made if appropriate, after the participant’s first week of exercise training, as part of the IE protocol fidelity assessment.

### Strategies to improve adherence to interventions

Participants will receive reminder text or email messages to help adherence to standard care advice collecting home blood pressure measurements and isometric exercise training.

A bespoke automated reminder system was developed in order to manage the different types of reminders and different periodicity of these.

Arm 1 (control) will receive monthly reminders to adhere to the standard care lifestyle advice given by their HCP at Baseline. Arm 2 (intervention) will also receive monthly standard care lifestyle advice in addition to three IE training reminders per week, for the duration of the study.

At follow up timepoints 4 weeks, 3 months and 6 months, all participants will receive a 24-h reminder to start taking their home blood pressure.

### Relevant concomitant care permitted or prohibited during the trial

Exclusion criteria states the participants should not be taking anti-hypertensive medications whilst taking part in the trial.

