## Abstract

**Background:**

Hypertension  (HTN) affects approximately 25% of the UK population and is a leading cause of mortality. Associated annual health care costs run into billions. National treatment guidance includes initial lifestyle advice, followed by anti-hypertensive medication if blood pressure (BP) remains high. However, adoption and adherence to recommended exercise guidelines, dietary advice and anti-hypertensive medication is poor. Four short bouts of isometric exercise (IE) performed 3 days per week (d/wk) at home elicits clinically significant reductions in BP in those with normal to high-normal BP. This study will determine the feasibility of delivering personalised IE to patients with stage 1 hypertension for whom lifestyle changes would be recommended before medication within NHS primary care.

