### Eligibility criteria

Patients aged 18+ with stage 1 hypertension who are not yet on anti-hypertensive medication and without any significant medical condition that would contraindicate their participation.

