### Exclusion criteria

Patients who are taking anti-hypertensive medication; have white coat hypertension (as evidenced by averaged home systolic BP < 135 mmHg); are unable to undertake the study intervention (isometric exercise); have a previous history of diabetes mellitus (type 1 or type 2), known or suspected ischaemic heart disease (including myocardial infarction and/or angina and/or coronary revascularization procedure), moderate or severe stenotic or regurgitant heart valve disease, atrial or ventricular arrhythmia, stroke or transient ischaemic attack, aortic aneurysm and/or peripheral arterial disease, uncorrected congenital or inherited heart condition; have an estimated glomerular filtration rate < 45 ml/min (calculated using CKD-EPI or MDRD formulae, and taking most recent documented results); have a documented left ventricular ejection fraction < 45% and/or left ventricular hypertrophy (by either echocardiography or standard ECG criteria, e.g. Sokolow-Lyon); have a documented urine albumin to creatinine ratio > 3.5 mg/mmol; are unable to provide informed consent; are enrolled in another Clinical Trial of an Interventional Medicinal Product or Medical Device or other interventional study; and if female, are pregnant or currently breast feeding. Then finally, any medical condition that, in the opinion of the investigator, would make the participant unsuitable for the study.

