### Provisions for post-trial care

The participants in the control arm will be offered an isometric exercise intervention after they have completed their time in the study. The GP practice will oversee participant’s general care throughout the trial and participants will be returned to the care of their GP after the trial.

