### Participant timeline

The participant timeline is presented in Table 1.

**Table 1 Tab1:** Participant schedule of events

Assessment	Remote screening assessment day 14	Study time point					
		Baseline assessment day 1 (remotely)	IIET visit (within 7 days of Baseline visit)	Follow up telephone call — IE arm only (within 7 days of IIET visit)	Assessment 2 day 28–33 (remotely)	Assessment 3 month 3 (± 7 days) (remotely)	Assessment 4 month 6 (± 7 days) (remotely)
Medical history	X	X					
Concomitant medication	X	X		X	X	X	X
Consent	X						
Observed blood pressure and heart rate		X			X	X	X
IE ability test	X						
Incremental IE test and IE programme provided (for those randomised to intervention arm only)			X				
AE review				X	X	X	X
Diet questionnaire		X			X	X	X
Exercise questionnaire		X			X	X	X
Quality of life questionnaire		X			X	X	X
Collection of IE exercise diary (for those randomised to intervention arm only)				X	X	X	X
Collection of home blood pressure and heart rate readings	X (between day 7 and day 1)	X		X	X	X	X
Health resource use questionnaire					X	X	X
IE experience questionnaire					X		

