### Sample size

Review of current literature revealed few IE studies in a hypertensive population. These studies were small (*n* < 25), conducted under different conditions to the proposed study, and showed low precision and large variability in estimates of the standard deviation (SD). A sample size of 100 participants, 50 per arm, will be used in the study. Allowing for 20% attrition and 6.5% incomplete data, 74 participants (37 in each arm) will have completed change measures at 4 weeks. This is in line with the recommended sample size of 70 to estimate key parameters from external pilot RCTs [62]. A sample size of 74 produces a two-sided 95% confidence interval with a width of 1.33 when the standard deviation is 4. This estimate of 4 has been taken from a previous study (*N* = 24) [10]. The sample size confidence interval has been calculated using Pass11 software (PASS 11. NCSS, LLC. Kaysville, UT, USA, www.ncss.com).

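### The concomitant-care section reports an entry criterion on anti-hypertensive medication as a ban throughout the trial, which, if applied literally, could remove participants because their blood pressure stayed high

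*Protocol article*

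**What the plan says.** Under Relevant concomitant care permitted or prohibited during the trial, the protocol article has one sentence: "Exclusion criteria states the participants should not be taking anti-hypertensive medications whilst taking part in the trial".

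The criteria it refers to read differently. Eligibility criteria admits adults with stage 1 hypertension "who are not yet on anti-hypertensive medication". Exclusion criteria lists "Patients who are taking anti-hypertensive medication". Neither mentions medication begun after randomisation.

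Four other places bear on the point:

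- The abstract describes national guidance as lifestyle advice first, "followed by anti-hypertensive medication if blood pressure (BP) remains high". The section on the choice of comparators gives the same order.
- Provisions for post-trial care leaves the practice in charge of participants' "general care throughout the trial and participants will be returned to the care of their GP after the trial".
- Strategies to improve adherence says that at week 4, month 3 and month 6 "all participants will receive a 24-h reminder to start taking their home blood pressure".
- Table 1 has a row for "Concomitant medication", marked at the week 4, month 3 and month 6 assessments alongside blood pressure.

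**The concern.** The concomitant-care sentence attributes to the exclusion criteria a rule that they do not contain, and it does so under the one heading where a site would look for the rule on treatment during follow-up. Starting medication is foreseeable here. Participants are untreated, have stage 1 hypertension, are followed for six months, and remain under a practice whose next step is a prescription if pressure does not fall. Taken literally, anyone who starts is in breach of an exclusion criterion. A site could respond by withdrawing that person or by putting off treatment that is indicated.

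If starters were withdrawn, three things would suffer:

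- Readings at months 3 and 6 would go missing because pressure was high. They feed primary outcomes: the variance of change, the systolic difference with its 80% and 95% intervals, and the definitive sample size.
- Attrition is counted as withdrawals from the study and is meant to inform future trials. It would include people who left only because of this sentence.
- The number who start medication would be harder to see. It is informative in itself, because the Discussion offers the exercise to patients who would rather avoid drug therapy.

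**Working it through.** **1. The texts side by side.** The eligibility wording (not yet on medication) and the exclusion wording (patients taking it) describe status when eligibility is judged. The concomitant-care sentence extends the condition to the whole of participation and names the exclusion criteria as its source. They have no such clause. The misattribution is therefore a matter of reading, with no arithmetic needed.

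**2. What happens to a starter.** The section on discontinuing or modifying interventions covers only the adjustment of the exercise prescription after the first week. No section orders withdrawal or discards readings. Table 1 and the reminders assume that follow-up goes on. The concomitant-care sentence is thus the only text that points towards removal, and it conflicts with the schedule.

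**3. The plan's own figure.** Sample size gives a 95% interval of width 1.33 for n = 74 and SD 4. The chi-square interval for an SD with 73 degrees of freedom runs from 3.44 to 4.77 (−13.9% to +19.3%), width 1.33, so the figure reproduces. The allowance "Allowing for 20% attrition and 6.5% incomplete data" gives 100 × 0.80 × 0.935 = 74.8, or 100 × (1 − 0.265) = 73.5, both consistent with 74. These figures refer to week 4 and are not in dispute.

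**4. Possible size at month 6.** The documents give no start rate, so every input below is an assumption.

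- Baseline systolic pressure N(147, 5); SD of change 4 or 8 mmHg; correlation between visits 0.3 or 0.7; true exercise effect −5 mmHg.
- The practice decides after week 4 and after month 3, on pressure measured with noise of SD 3.
- The threshold is set so that 5, 10 or 20% of controls start, and is the same in both arms. In the exercise arm 0.9–8.5% then start.
- Month 6 readings of starters are lost with probability 0.5 or 1. The difference comes from ANCOVA on baseline, with 400,000 simulated per arm.

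| Starters lost | Difference diluted by (mmHg) | SD too low by | Extra withdrawals per 100 |
|---|---|---|---|
| Half | 0.03–0.37 | 0.1–2.4% | 1.5–7.1 |
| All | 0.07–0.94 | 0.2–6.1% | 2.9–14.2 |

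For SD 8, correlation 0.7 and 10% of controls starting, the dilution is 0.25 mmHg (half lost) or 0.58 mmHg (all lost).

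**5. Scale.** With 37 per arm the 80% half-width for the difference is 1.2816 × SD × √(2/37), which is 1.19 mmHg at SD 4 and 2.38 mmHg at SD 8. The largest dilution in the table, 0.94, is below both. The largest fall in the SD, 6.1%, is inside the −13.9% sampling limit.

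**6. A harsher bound.** Suppose instead that everyone above the control arm's 90th, 80th or 70th percentile of change is removed, with SD 4 and a true difference of −4 mmHg. The observed difference becomes −3.33, −2.89 or −2.55, so the dilution is 0.67, 1.11 or 1.45 mmHg. The pooled SD falls to 3.62, 3.39 or 3.19. The last dilution exceeds 1.19, and the last two SDs fall below 3.44. This rule removes people mechanically on the outcome itself, so it is an outer bound and not a forecast.

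**7. The alternative.** In the set-up of step 4, keep every reading and assume that the drug lowers systolic pressure by 5–10 mmHg. The difference is then diluted by 0.2–1.4 mmHg, and the SD ratio runs from 0.929 to 1.221.

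**The case against.** The strongest reply is that this is a wording slip in a condensed article. The exclusion line carries no explicit time limit, a trial in unmedicated patients may legitimately bar these drugs during participation, and the operative procedures (Table 1, reminders to all, practice oversight) already point to continued follow-up. Some of the detail requested below might sit in the full protocol. Retention is also no clear gain for the estimates: under the assumptions used, keeping on-medication readings can dilute the difference by more than losing them.

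Much of this stands. A reader might infer that the plan withdraws anyone who starts medication, or that its month 3 and month 6 estimates are biased. The documents support neither. No section states a withdrawal, and the bias depends on start rates and site behaviour that the article does not give. Nor does any section tell a practice to withhold treatment. The size calculation also models complete loss at month 6 only. It does not cover the secondary intention-to-treat analysis, which fills missing values by last or baseline observation carried forward.

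What the reply does not remove is the misattribution. The article states a rule, assigns it to criteria that lack it, and sets it against its own schedule. That is a wrong statement and more than an omitted detail. Readings that are kept can still be set aside in the analysis, whereas readings never taken cannot be recovered.

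**Conclusion.** The point holds as a misstatement with a conditional consequence. The criteria apply at entry, and the concomitant-care section wrongly says that they cover the whole of participation. If a site followed it literally, readings at months 3 and 6 would be lost in a way related to the outcome, exits made by the rule would be counted as attrition, and indicated treatment might be delayed.

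The size cannot be derived from the documents. Under the noisy-decision assumptions with 5–20% of controls starting, the bias is below sampling error in every case run. Only the mechanical bound exceeds it. The effect on attrition is the more noticeable one: up to 14.2 per 100 by month 6 if every starter left, against a 20% allowance that was itself set for week 4. The week 4 results are little affected. This is a cheap improvement, not a flaw that undermines the study.

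**What to change.** Rewrite the concomitant-care sentence so that the medication criterion applies at entry only, in line with the eligibility and exclusion sections. Then add that:

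- starting clinically indicated anti-hypertensive medication is the practice's decision and not a reason for withdrawal;
- participants who start stay in their randomised arm and in the blood pressure and medication follow-up already in Table 1, with the drug and its start date recorded;
- starts are counted separately from withdrawals.

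The cost is two or three sentences and no added visit. The downside is that some readings will be taken on medication and can themselves dilute the difference, so retention does not remove bias by itself. It preserves the readings and the medication record. How on-medication readings are analysed can be left to the SAP.

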### Provisions for post-trial care

The participants in the control arm will be offered an isometric exercise intervention after they have completed their time in the study. The GP practice will oversee participant’s general care throughout the trial and participants will be returned to the care of their GP after the trial.

### Outcomes

#### Primary

Feasibility of isometric exercise prescription assessed using qualitative data from healthcare professional focus groups at month 11/12 of 18 month studyFeasibility of isometric exercise intervention and study assessed using qualitative data from participants at month 7 and 11 of 18 month studyVariance of blood pressure changes from baseline using participant blood pressure data at week 4 and months 3 and 6 of interventionSample size for a definitive randomised controlled trial, calculated using estimate of variability of evidence of effect on systolic blood pressure change at week 1 and months 3 and 6 (of the intervention) from the feasibility study and the minimum clinically important differenceEstimate of the treatment difference in systolic BP change from baseline and 80 and 95% confidence intervals to provide preliminary assessment of benefit, and aid decision whether to proceed to a confirmatory RCT at the end of the feasibility study

#### Secondary

Fidelity of the isometric exercise prescription measured using prescription competency assessment data (ability to carry out incremental isometric exercise test and an accurate prescription of individual IE intensity - knee joint angle translated into bend and squat measurements) from HCP intervention training at month 3 of 18 month studyFidelity of the delivery of the isometric exercise prescription by HCP assessed through observation (study coordinator) of the first Incremental Isometric Exercise Test (IIET) and subsequent prescription delivered at site from month 3 to month 5 of 18 month studyFidelity of the isometric exercise prescription defined by participant 95% peak heart rate falls within their THRR in at least two-thirds of all training sessions at say 7–10 of interventionShort and medium-term adherence rates recorded as those adhering to isometric exercise intervention at week 4, month 3 and month 6 of intervention5.Recruitment and attrition rates from data collected at sites at month 10 and month 15 of 18 month study6.GPs and healthcare professionals’ attitudes to isometric exercise as a treatment option for patients, measured using remote focus groups and telephone interviews at month 11/12 of 18 month study7.Cost and cost-utility of the isometric exercise intervention using healthcare resource use data and quality-adjusted life years (QALYs) at month 15 (or last patient follow up) of 18 month study8.Participant experiences of undertaking isometric exercise using participant isometric exercise experience surveys at week 4 of intervention9.
*Effect of COVID-19 on recruitment rates and participation using participant focus groups or telephone calls at month 7 and 11 of 18 month study*
10.
*Feasibility of using observed home blood pressure readings for remote blood pressure monitoring, using participant blood pressure data and observations from the measures at day 1, week 4, month 3 and month 6 of intervention*

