### Data collection and management

#### Plans for assessment and collection of outcomes

The success of intervention delivery by healthcare professionals in a primary NHS healthcare settings will be determined using both qualitative data (*remote*) and the heart rate data recorded by the participants at the end of each isometric wall squat bout x4 per session over the 3 sessions completed in the first week using a wireless heart rate monitor and chest strap (Sigma PC 15.11, Neustadt/Weinstraße, Germany). The average HR calculated from the first 3 sessions will then be compared against the individuals’ target training HR (calculated as 95% of HR_peak_ measured during the individuals incremental isometric exercise test IIET) with an acceptable target heart rate range (THRR) of 76–111% of heart rate peak [60]. Perceptions of intervention delivery by healthcare professionals will be explored in qualitative focus groups (*remote*). The focus group questions for both healthcare professionals and participants were guided by the work of O’Cathain et al. [64] on the use of qualitative research in feasibility studies for randomised controlled trials. The groups will discuss the intervention content and delivery and the trial design, conduct and processes. For professionals, the core questions will be the following: What are your views on how the isometric exercise was implemented? Is the study design acceptable? How did the planned recruitment practices work in practice? Are the proposed process and outcome measures valid for this group of service users?

Any change in BP following the IE intervention will be determined using the *home blood pressure data* (measured using an automated upper arm blood pressure monitor [Omron M3 Intellisense, Kyoto, Japan] at weeks 4, 12, and 24) recorded in the participants diaries and comparing this against their *observed* baseline (recorded at day 1). This data will also be used to estimate BP variance by calculating systolic BP change from baseline at each endpoint. An estimate of the difference in change from baseline between the isometric exercise and control group will be calculated with 80% and 95% confidence intervals.

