Accuracy of IE protocol delivery will be determined using data from three fidelity assessments; the first being healthcare professional competency checks administered during their isometric exercise prescription training; the second being expert observation/evaluation of at least the first IIET delivered by each HCP; and then finally, by third party examination of the first week of heart rate data recorded in the study diaries of each HCP’s specific participants, with average HR calculated from the first 3 sessions being compared against the individuals target training HR as described above.

Execution of the IE training protocol in the home will be assessed for each individual participant at the end of the first week by checking to see if their mean training heart rate per week falls within target heart rate range/reference interval (76–111%) *data for weeks 4, 12 and 24 will now be assessed at the end of the 6-month training period*. An estimate of the short- (4 week) and medium-term (3 and 6 month) adherence rates to IE training will be based upon the data collected from participant diaries to calculate the proportion of participants completing ≥ two thirds of all IE sessions (12, 36 and 72) at each time point respectively. Patient recruitment and participant attrition rates will be calculated based upon the average number of participants recruited per week over the 7 month recruitment period and the number of withdrawals from the study once the last follow-up call to the last participant has been made.

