Participant experiences of IE will be assessed through a quantitative online survey conducted at week 4. All participants receiving the IE intervention will be invited to take part in one of two focus groups (*remote*) to draw out respondents’ attitudes, feelings, beliefs, and experiences regarding the intervention [65]. The core focus group questions for participants were also directed by the guidelines for using qualitative research in feasibility studies [64]. What are your views on how you applied the isometric exercise intervention? What are your thoughts on how the study was conducted? What do you think are important outcomes to consider in a full trial? *This will also be used as an opportunity to explore possible negative effects of COVID-19 on recruitment rates and participation*. These groups will be held at month 4 and month 8 of the recruitment period with 6–8 participants in each group. One focus group will also be undertaken with healthcare professionals involved in the intervention delivery at the end of the recruitment period to explore views and experiences of the IE intervention. Lay and professional members of the research team will co-produce the topic guide and co-facilitate the focus groups. The focus groups are proposed to last for between 60 and 90 min. The groups will be digitally recorded and transcribed. Telephone interviews (*n* = 5–10) will be conducted with stakeholders from GP practices which are not recruitment sites and not involved in the intervention delivery to explore the willingness of GPs and primary care healthcare professionals to consider IE as a viable treatment option for patients, including barriers and facilitators for delivering and integrating this within an NHS care pathway for hypertension.

The economic evaluation of delivering the IE intervention will be calculated once the last follow-up call has been made to the last participant and will be estimated from Healthcare resource use data and quality-adjusted life years (QALYs). Since QALYs are the primary outcome of the economic evaluation, utility values will be obtained from patients’ responses to each of the EQ-5D-5L at the beginning of the intervention and at week 4 and months 3 and 6 after the intervention [66, 67].

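### Secondary outcome 9 looks for the effect of COVID-19 on recruitment by asking only people who were recruited

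*Protocol article*

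**What the plan says.** The Secondary outcomes list in the protocol article gives outcome 9 as "Effect of COVID-19 on recruitment rates and participation using participant focus groups or telephone calls at month 7 and 11 of 18 month study". In Objectives, the same aim is added to the objective on participants' experience of the exercise and is framed as exploratory.

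Under Plans for assessment and collection of outcomes, the groups are described as follows.
- Who is invited: "All participants receiving the IE intervention will be invited to take part in one of two focus groups".
- When, and how many: "These groups will be held at month 4 and month 8 of the recruitment period with 6–8 participants in each group".
- The COVID-19 question: "This will also be used as an opportunity to explore possible negative effects of COVID-19 on recruitment rates and participation".

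Recruitment itself is a separate secondary outcome (number 5). It is taken from site data and calculated as the "average number of participants recruited per week over the 7 month recruitment period". The Recruitment section says that patients are found by database search and invited, and that the study is also advertised through practices, websites, social media, newsletters and text messages. Objectives and Discussion both say that recruitment rates from this study will inform the definitive trial.

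**The concern.** COVID-19 would lower recruitment mainly through people who heard of the study and did not join. The informants named for outcome 9 all joined, and did so during the pandemic. They are selected on the very thing being studied, and interviewing more of them would not remove that selection.

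What is at stake is how the recruitment rate is read when it is carried forward. If recruitment is slow, the team will want to know whether the cause was temporary (the pandemic) or lasting (the exercise, the randomisation, the trial procedures). Deterrence is plausible on the plan's own schedule: Table 1 makes screening, baseline and follow-up remote, while exercise-arm participants must attend the surgery for the incremental test. Enrolled people who report little worry about that visit tell us little about those who stayed away.

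**Working it through.** The plan states no figure for this outcome, so there is none to reproduce. The check is to trace each source that could inform it, and then to show on assumed numbers what the stated source cannot separate.

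**1. Are the telephone calls also with participants?** Outcome 9 attaches the word participant to the groups and leaves the calls unspecified. The second primary outcome collects qualitative data from participants at the same study months, 7 and 11. The only other telephone interviews described are those with outside stakeholders, which secondary outcome 6 places at month 11/12. The calls in outcome 9 are therefore best read as calls with participants.

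**2. Who can speak to recruitment?**

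| Source | Named for outcome 9? | Reaches decliners? |
|---|---|---|
| Participant focus groups (exercise arm) | Yes | No |
| Participant telephone calls | Yes | No |
| Weekly recruitment count (outcome 5) | No | No; a count with no stated number invited and no reasons |
| Healthcare professional focus group, asked "How did the planned recruitment practices work in practice" | No | No; second-hand, and not tied to COVID-19 |
| Stakeholder interviews, which "will be conducted with stakeholders from GP practices which are not recruitment sites and not involved in the intervention delivery" | No | No; they concern willingness to use the exercise |

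**3. Number of informants.** Focus groups: 2 × 6 = 12 to 2 × 8 = 16 people, which is 12/50 = 24% to 16/50 = 32% of the planned exercise arm. The number of participant calls is not stated, so 16 is not an upper limit. The number of decliners among those asked is 0, however many calls are made.

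**4. Illustration (all inputs assumed except the target of 100 recruited).** Let A be the number approached and q the share of decliners who refused because of COVID-19. Observed uptake is 100/A. If all those people would otherwise have joined, uptake without COVID-19 is (100 + q(A − 100))/A.

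| A | Observed | q = 0 | q = 0.25 | q = 0.50 |
|---|---|---|---|---|
| 200 | 50% | 50% | 62.5% | 75% |
| 500 | 20% | 20% | 40% | 60% |
| 1000 | 10% | 10% | 32.5% | 55% |

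For example, with A = 500 and q = 0.25: (100 + 0.25 × 400)/500 = 200/500 = 40%. Within each row the same 100 people are enrolled, so the groups, the calls and the average weekly count are all compatible with every column. The table shows what cannot be distinguished. It does not estimate any actual effect.

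**The case against.** The best defence is that this is a qualitative aim. Objectives and the assessment section speak of exploring, the analysis is thematic, and only the one-line outcome label reads like an effect to be estimated. Enrolled people can describe their own hesitation when approached, and the healthcare professionals' group may well bring up pandemic barriers. This is why the point is minor. It does not make acceptors a source on why others declined, and the professionals' group is not assigned to this outcome.

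A second defence is that an article condenses the full protocol, which may hold a screening log with reasons for declining. That is fair, and the absence of a log from the article is not the point made here. The article assigns a particular source to a particular outcome, and that source does not fit the recruitment part. If a log exists, it only has to be named.

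Three stronger readings may tempt a reader, and the article supports none of them.
- That outcome 9 cannot be measured at all. It also covers participation, on which enrolled people are a proper source.
- That at most 16 people will inform it. The calls have no stated number.
- That the study would wrongly conclude that COVID-19 had little effect. No such inference or decision rule is stated, and nothing says that the recruitment rate will be adjusted using focus group views.

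**Conclusion.** The point holds for the recruitment part of outcome 9 only. The stated source is confined to people who accepted, so it records their perceptions and could mislead about COVID-19 as a barrier to joining. No decliners are asked under the methods stated for this outcome.

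The practical effect cannot be sized from the article, because it gives neither the number approached nor any refusal rate. The 20% to 60% range for 500 approached rests on assumed inputs, and on the assumption that everyone refusing because of COVID-19 would otherwise have joined. Severity is minor: this is an exploratory secondary outcome, the weekly recruitment rate is still obtained, and the objective on variance of blood pressure change is unaffected.

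**What to change.** Add one optional coded item on the reason for not taking part, with COVID-19 concern as one of the codes, to the invitation reply and the site screening log. If the full protocol already has such a log, name it as the source for the recruitment part of outcome 9. Report numbers invited, declined, and declined for COVID-19, by site and calendar month, beside the weekly recruitment rate. Keep the focus groups and calls for the effect on participation.

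The cost is a minor amendment, one tick-box and one table. Reasons will be incomplete: people who do not reply, or who ignore an advert, are not captured. The COVID-19 count should therefore be presented as partial and read as a lower bound.

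If no new data can be collected, the least that is needed is to reword the recruitment part of outcome 9 as enrolled participants' perceptions of COVID-19 and recruitment. That costs nothing.
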